#### Secondary endpoints

Secondary endpoints (∆ EQ-5D-5L, ∆ DIAB-Q, ΔDDD ATC A10B, ∆ blood pressure, ∆ body composition, PREM) will be analyzed in a similar way taking into account different types of dependent variables and respective techniques, e.g., Wilcoxon-Mann–Whitney test for non-parametric data. Similar to the primary evaluation, the main model will be the mixed-effects model in which we will control for patient characteristics such as baseline outcome parameter value (e.g., EQ-5D-5L), BMI, gender, age and comorbidities as fixed effects, and incorporate clusters (practices) as random intercepts to also account for potential cluster effects. In addition, we will not control for randomization covariates. In analogue, we use the Wald Test or the Likelihood Ratio Test to evaluate hypotheses on fixed and random effects.

The cost-effectiveness analysis (CEA) will use ∆HbA1c as effect measure and costs evaluated from payer perspective including costs for all relevant treatments and drugs throughout the observed patient pathway at 12 and 18 months (see Appendix A, tab Groupe Mutuel). We further account for the cost of the intervention. The CEA will be performed in accordance with the consolidated standards for health economic evaluation reports (CHEERS 2022) [37]. The CEA will only be conducted for the participants that are insured at Groupe Mutuel due to data availability. In the case that the cost data are heavily right skewed, we will, as sensitivity analysis, perform a 95% winsorization on the cost data and repeat the CEA.

Analyses will be carried out using R, Stata, or Microsoft Excel as required.

### Interim analyses {21b}

No formal interim analyses are planned. However, we assess the adherence of both physicians and patients to the study protocol. This includes checking the consistency of data entries by physicians into the study software and monitoring patient participation rates in completing PROMs and adhering to intervention protocols. This analysis helps identify participation barriers and enables the implementation of strategies to enhance engagement and compliance.

### Methods for additional analyses (e.g., subgroup analyses) {20b}

Heterogeneity of treatment effect analysis will be applied to estimate treatment effects in clinically relevant subgroups and to identify which individual might benefit from the intervention. We will perform subgroup analyses for the following variables, as we hypothesize differential effects:◦Gender: male vs. female◦Age: below/above median age◦BMI: below/above 30 (obesity)◦A10B DDD: below/equal to/above the mean number of DDD on the same time base◦Baseline EQ-5D-5L score: below/above median baseline score◦Baseline score DIAB-Q: below/above the median baseline score

We will use a causal forest approach to estimate mean conditional treatment effects (see also [38]). We control for the same patient characteristics as in the mixed-effects model (e.g., baseline HbA1c, BMI, gender, age, comorbidities) but omit the subgroup variable as a control. In the event that the sample size is insufficient to use a causal forest approach, we will implement the mixed-effects model, including a subgroup dummy variable and an interaction term [39].

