#### Primary endpoint

HbA1c will be analyzed with common descriptive statistics, i.e., sample mean, median, minimum, maximum, standard deviation, and interquartile range. We will follow the intention to treat principle, i.e., all included patients who did not withdraw consent will be analyzed. We will apply two-sample (independent samples) t-tests or Wilcoxon-Mann–Whitney tests (depending on distribution) for the primary endpoint for the mean differences at baseline, month 12 and month 18 and changes in mean difference from baseline to 12 and 18 months. As we anticipate cluster effects at the practice level due to the randomization method, our main model for the assessment of the primary endpoint will be a mixed-effects model. We will control for patient characteristics at baseline (e.g., baseline HbA1c, BMI, gender, age, comorbidities, diabetes duration) as fixed effects, which are likely to affect the primary endpoint. In addition, we will incorporate practice as a random intercept in the model to account for potential cluster effects at the practice level. We will not control for covariate-restricted randomization variables, as differences between practices are accounted for by random intercepts. We use the Wald Test or the Likelihood Ratio Test to evaluate hypotheses on fixed and random effects.

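### In the fallback subgroup model, cutting age, BMI and baseline scores into two groups gives a weaker test of a gradual change in effect than a continuous interaction would

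*Protocol article*

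**What the plan says.** Section {20b} of the protocol article introduces the list of modifiers thus: "We will perform subgroup analyses for the following variables, as we hypothesize differential effects". Besides gender and antidiabetic drug doses, the list contains four measures that are continuous or scored:

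- age, "Age: below/above median age"
- BMI, cut at 30 and labelled as obesity
- EQ-5D-5L, "Baseline EQ-5D-5L score: below/above median baseline score"
- DIAB-Q, "Baseline score DIAB-Q: below/above the median baseline score"

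The first-line method is clear: "We will use a causal forest approach to estimate mean conditional treatment effects". The mixed model applies only if the sample is insufficient for the forest; in that case "we will implement the mixed-effects model, including a subgroup dummy variable and an interaction term". No threshold for insufficiency is given, and no interaction with an uncut modifier is mentioned.

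The uncut values will be at hand. The main model under Primary endpoint states "We will control for patient characteristics at baseline (e.g., baseline HbA1c, BMI, gender, age, comorbidities, diabetes duration) as fixed effects". EQ-5D-5L and DIAB-Q are collected at baseline in both arms.

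**The concern.** The section expects the effect to differ by these characteristics and wants to find out who benefits. A two-level split compares the average effect in one half with the average effect in the other. It ignores where a patient lies within a half. If the effect changes gradually with age or with a score, the split uses only part of the available information.

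The fallback would be used because data are scarce, which is when this loss matters most. A real gradient would more often be missed, and the result could then be read as a uniform effect.

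The protocol gives no clinical reason for a cut at the median. Read in the natural way as the median of the enrolled sample, the cut also depends on who enters the trial, so it is awkward to carry into the wider roll-out that the trial is meant to inform. BMI 30 is different in this respect, because it is tied to a named clinical category.

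**Working it through.** **Inputs from Sample size {14}.** Effect 0.58 percentage points; SD 1.10; ICC 0.032; average cluster size 5 with coefficient of variation 0.30; alpha 5% (two-sided assumed); power 80%; drop-out 15%; 154 patients recruited.

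**The plan's own figure.** Patients per arm without clustering: 2 × [1.10 × (1.960 + 0.842) / 0.58]² = 56.46. Design effect: 1 + [(1 + 0.30²) × 5 − 1] × 0.032 = 1.1424. Product: 64.5 per arm, or 12.9 clusters of 5, rounded up to 13 clusters (65 patients) per arm. For drop-out: 65 / 0.85 = 76.5, rounded up to 77 per arm, 154 in all. The plan's figure reproduces. Analysed patients: 154 × 0.85 = 131.

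**Information kept by a cut.** For a linear interaction, the efficiency of the dummy relative to the continuous modifier X is the squared correlation between X and its dummy: p(1 − p) × (mean of X above the cut − mean below)² / Var(X).

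- Uniform X, median cut: 0.75, a loss of 25%.
- Normal X, median cut: 2/π = 0.637, a loss of 36%.

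On the 130 patients in 26 clusters of 5, this equals about 97 and 83 patients.

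**Power.** The protocol states no interaction size, so a range is used. Let D be the difference in treatment effect between the upper and lower half. With four equal cells, SE = 1.10 × √(16/131) = 0.384. The split z is D/SE. Under linearity the continuous z is the split z divided by √0.637 = 0.798 (normal) or √0.75 = 0.866 (uniform).

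| D | Split | Continuous, uniform | Continuous, normal |
|---|---|---|---|
| 0.29 | z 0.75, 12% | z 0.87, 14% | z 0.95, 16% |
| 0.58 | z 1.51, 33% | z 1.74, 41% | z 1.89, 47% |
| 0.87 | z 2.26, 62% | z 2.61, 74% | z 2.84, 81% |

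**Check with clustering.** A simulation with 26 clusters of 5, ICC 0.032 and 4,000 runs gave, split against continuous:

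- D = 0.58: 34% against 47% (normal), 32% against 40% (uniform)
- D = 0.87: 60% against 78% (normal), 62% against 74% (uniform)

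Type I error was about 5% for both tests.

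**If the effect steps exactly at the median.** The ranking reverses, and the continuous z is the split z multiplied by 0.798 or 0.866.

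- D = 0.58: z = 1.51 × 0.798 = 1.20 or 1.51 × 0.866 = 1.31, so power is 23–26% against 33% for the split.
- D = 0.87: z = 1.81 or 1.96, so power is 44–50% against 62%.

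**Outside the 25–36% range.** These losses use assumed distributions under linearity, because the protocol gives none.

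- BMI cut at 30: 36% for mean 30, SD 5; 40% for mean 28, SD 5; 42% for mean 33, SD 6; 48% for mean 27, SD 4; 51% for mean 35, SD 6.
- Skewed scores cut at the median: 39% for Beta(4,1), 46% for Beta(9,1), 52% for an exponential shape.

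**The case against.** A reader might infer that the dummy-by-arm interaction is the planned heterogeneity test. It is not: the causal forest comes first and the interaction model is conditional. The efficiency and power figures therefore apply only to the fallback. What remains is that the fallback is plausible at this sample size, and that the same cut groups define the reported effects under either method.

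A reader might also take 25–36% as a property of this trial, covering all four modifiers. The documents give no modifier distributions and no shape of effect modification. The range needs a median cut, a linear change in effect and a uniform-to-normal modifier. It does not describe BMI cut at 30 or strongly skewed scores, and a step at the cut reverses it.

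The larger gains also need large interactions. D = 0.58 equals the whole assumed treatment effect, and D = 0.87 is 1.5 times it. At 0.29 both tests have little power. A non-significant interaction in this trial cannot show a uniform effect under either approach.

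Obesity is a recognised category, and one stated aim is to report effects in clinically relevant subgroups, which a split serves. The treatment of patients exactly at the median is a coding detail that a full analysis plan can settle. These objections limit the weight of the point. They do not remove the gain, because the splits can stay for presentation while the test uses the uncut values.

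**Conclusion.** The point holds as a minor improvement to the fallback mixed model. Under roughly linear modification, a median cut there loses about 25% to 36% of the information on the interaction for a uniform to normal modifier. With 131 patients, SD 1.10 and a two-sided 5% test, that means 33% power against 41–47% for a between-halves difference of 0.58, and a gain of only 2–4 percentage points at 0.29. For BMI at 30 and for skewed scores the loss depends on their distribution and may be larger. Nothing in the protocol points to a step at a median, but if there were one the split would be the better test.

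It would go too far to say that the continuous test makes these analyses well powered. They stay weak unless the interaction is very large. These are additional analyses, so the primary endpoint, its main model and the sample size are unaffected.

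**What to change.** In {20b}, leave the causal forest as the first method. For the fallback mixed model, state that heterogeneity by age, BMI, baseline EQ-5D-5L and baseline DIAB-Q is tested by the arm-by-modifier interaction. Enter the modifier as a centred continuous variable, with its main effect and the interaction, and keep the random intercept for practice. Report the estimated treatment effect with 95% confidence intervals at modifier values named in advance. Fixed values are easier to carry to other patients than sample percentiles. Keep the median splits and the BMI 30 split as descriptive display. Gender stays binary.

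The cost is a wording change, with no new data. The downside is the assumption of an approximately linear change in effect. The plan should say how this will be checked, for example by residual plots or against the descriptive split results.

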### Methods in analysis to handle protocol non-adherence and any statistical methods to handle missing data {20c}

The intention-to-treat principle will be followed. All included patients who have not withdrawn their consent will be analyzed. Multiple imputation techniques such as Random Forest Imputation (MissForest) will be used [40]. Drop-outs will not be considered in the final analysis. In the event of withdrawal, patients will not be replaced.

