### Criteria for discontinuing or modifying allocated interventions {11b}

At any time, patients can withdraw from the study. Their data will then be deleted and excluded from study evaluation. Patients will not be allowed to switch between intervention and control group.

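### The missing-data section claims intention to treat and imputation but also leaves drop-outs out of the final analysis, so the primary analysis set is contradictory unless drop-out means only withdrawal of consent

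*Protocol article*

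**What the plan says.** The primary endpoint paragraph of {20a} defines the principle: "We will follow the intention to treat principle, i.e., all included patients who did not withdraw consent will be analyzed". Section {20c} repeats it: "The intention-to-treat principle will be followed. All included patients who have not withdrawn their consent will be analyzed". It then names multiple imputation, with random-forest imputation as the example, but does not say which patients or variables this covers. The next sentence reads "Drop-outs will not be considered in the final analysis", followed by "In the event of withdrawal, patients will not be replaced".

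Sections {26a} and {11b} both govern patients who leave the study: "Their data will then be deleted and excluded from study evaluation". Neither separates a patient who stops the programme's activities from one who leaves follow-up.

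Section {14} plans for 15% drop-out, counted to the end of the trial period, and raises recruitment to 77 per arm on that account.

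**The concern.** Three statements in one short paragraph do not fit together on their plain meaning: analyse everyone who has not withdrawn consent, impute missing values, and leave drop-outs out. The patient who matters is the one who has not withdrawn consent but has no month-12 HbA1c. The first two statements keep that patient and the third removes them. Two statisticians could build different primary analysis sets from the same text.

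If the third statement governs, imputation never reaches the missing primary outcomes of those who left, and the comparison is restricted to patients who stayed. It would then depend on whether leaving is related to arm and to HbA1c. Practices know their allocation, and the two arms differ in what is asked of and offered to patients, so such a relation cannot be ruled out.

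**Working it through.** **1. How many patients are at stake.** Inputs from {14}: difference 0.58 percentage points, SD 1.10, intraclass correlation 0.032, cluster size 5, coefficient of variation 0.30, alpha 5% (taken as two-sided), power 80%, drop-out 15%.

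- Individually randomised size per arm: 2 × [1.10 × (1.96 + 0.84) / 0.58]² = 56.5 (computed with unrounded normal quantiles)
- Design effect: 1 + [(1 + 0.30²) × 5 − 1] × 0.032 = 1.1424
- Per arm: 56.46 × 1.1424 = 64.5, or 12.9 clusters of five, rounded up to 13 clusters = 65 patients
- With drop-out: 65 / 0.85 = 76.5, so 77 per arm and 154 in total

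This reproduces the plan's figure. The sample size is not in error on this point. It implies 154 × 0.15 = 23.1 drop-outs and 154 × 0.85 = 130.9 patients remaining.

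**2. The rules applied to each type of patient.**

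| Patient | Drop-out read broadly | Drop-out = consent withdrawn |
|---|---|---|
| Stays, month-12 HbA1c recorded | Analysed | Analysed |
| Stops activities, still measured at month 12 | Analysed (no text excludes for non-adherence) | Analysed |
| Consent not withdrawn, lost, no month-12 HbA1c | Included by one sentence, excluded by another | Analysed, value imputed |
| Withdraws from the study | Excluded, data deleted | Excluded, data deleted |

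The conflict is confined to the third row. The fourth row departs from full intention to treat on either reading.

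**3. What exclusion could do under no true effect (assumptions, not document figures).** Let drop-outs end s points worse than completers in both arms, with drop-out proportions p1 (intervention) and p0 (control). The completers' mean in an arm is then its overall mean minus p × s. The spurious difference is s × (p1 − p0), favouring the arm that loses more.

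| Drop-out, intervention vs control | s = 0.25 | s = 0.5 | s = 1.1 |
|---|---|---|---|
| 15% vs 15% | 0 | 0 | 0 |
| 20% vs 10% | 0.025 | 0.05 | 0.11 |
| 25% vs 5% | 0.05 | 0.10 | 0.22 |

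For scale, the plan's inputs give a standard error of 1.10 × √(1.1424 × 2 / 65) = 0.21 points. The 20% versus 10% row therefore runs from about 0.1 to about 0.5 of one standard error.

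**The case against.** The best defence is that a drop-out here is simply someone who withdrew consent. The sentence stands between two others about withdrawal, and {26a} and {11b} remove withdrawn patients anyway. On that reading the paragraph is consistent and consenting patients with missing HbA1c are imputed. This is possible, but the text does not say it. Drop-outs have a sentence of their own, which would then only repeat the one before. The inflation in {14} does not settle the meaning, because any plan inflates for missing outcomes.

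Several stronger readings are tempting but not supported:

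- **That the result is a comparison of engaged intervention patients with controls.** Nothing excludes a patient for poor adherence. The treatment plan is voluntary and adaptable, and a patient who does little but stays in the study is analysed.
- **That patients know their arm and that selection favours the programme.** Section {17a} calls the trial single-blinded and relies on arm-specific patient information. Intervention patients carry more tasks, but they also get free services and active follow-up by the study manager, which could lower their drop-out. The direction cannot be derived.
- **That the effect is overstated by 18%.** If completers gain 0.58 and intervention drop-outs gain nothing, the all-enrolled effect is 0.85 × 0.58 = 0.493, and 0.58 / 0.493 = 1.18. This rests on an assumed zero gain. A mixed model or standard multiple imputation, which assumes data missing at random, would not close that gap.
- **That deletion rules out every sensitivity analysis.** Counts by arm can be kept, and analyses of non-withdrawn patients with missing data remain possible.

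The 15% also runs to the end of the trial, whereas the primary endpoint is at month 12, so 23 is better read as an upper figure.

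**Conclusion.** The point holds as a contradiction in the definition of the primary analysis set. Read literally, {20c} omits consenting patients whose missing month-12 HbA1c should be treated as missing data, and that is not intention to treat. Read narrowly, the paragraph is consistent but relies on a definition it does not give. On both readings withdrawn patients are excluded and their data deleted, so unqualified intention to treat claims more than the plan delivers.

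Up to about 23 of 154 patients are affected, on the plan's own 15%. The spurious difference of 0.025 to 0.11 points under no effect rests on the assumed 20% versus 10% drop-out and outcomes 0.25 to 1.1 points worse among drop-outs. Equal, non-selective drop-out would give little bias. The documents fix neither size nor direction. The case for correction rests on the contradictory rule, which is cheap to resolve before final data.

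**What to change.** In {20c}, delete the drop-out sentence. State that every enrolled patient who has not withdrawn consent is analysed in the arm to which the practice was allocated. A missing month-12 HbA1c should be handled by the mixed model or by proper multiple imputation that accounts for practice. In {20a} and {20c}, describe the set without withdrawn patients as modified intention to treat. Report the numbers lost and the numbers withdrawn by arm.

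For future consents only, and subject to ethics approval, amend {11b} and {26a} to separate stopping the programme, after which follow-up continues, from withdrawing from the study. Data collected up to withdrawal would be kept unless the patient asks for deletion. Deletion promises already given must be honoured. Recruitment was due to end around 31 December 2025, so this part may reach few patients or none.

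A delta-adjusted sensitivity analysis by arm would be a useful addition, but its absence here is not an error, since it may be left to an analysis plan.

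The cost is a wording amendment and a little more analysis work. No extra patients are needed. The consent change also needs ethics review.

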### Plans to give access to the full protocol, participant level-data, and statistical code {31c}

The protocol for our study will be made publicly available upon completion. Patient-level data will not be publicly available due to data privacy regulations. The statistical code used in our analysis will be available upon request.

## Oversight and monitoring

### Composition of the coordinating center and trial steering committee {5d}

The steering committee for the study consists of the principal investigator team from Réseau Delta, a responsible from the project sponsor Groupe Mutuel, the CEO of the study software SOKLE, and the academic director of the School of Medicine of the University of St. Gallen.

### Composition of the data monitoring committee, its role and reporting structure {21a}

Data and study adherence monitoring is done by the principal investigator (see Monitoring Plan in Appendix C). The study manager sends bi-weekly statistics on recruitment numbers, data entry quality, and PROM questionnaire response rates to the University of St. Gallen. The study manager in cooperation with the University of St. Gallen prepares bi-monthly reports to the steering committee to potentially initiate adaptations or other actions.

### Adverse event reporting and harms {22}

Although no adverse events or harms are expected to be caused by the intervention of this study, all adverse events and harms are documented and immediately (within a maximum of 24 h) reported to the steering committee. If it cannot be ruled out that an adverse event occurring in Switzerland is attributable to the intervention, the principal investigator reports it to the responsible Ethics Committee within 15 days.

### Frequency and plans for auditing trial conduct {23}

The detailed monitoring plan for the study (see Appendix C) implements a Risk-Based Monitoring strategy to ensure study quality and compliance, with centralized verification of source data, notably via extractable source data (according to time and date) from measuring devices (notably HbA1c levels). Remote opening, routine, and closing visits are scheduled as necessary to ensure protocol compliance, with direct access to data for the sponsor and ethics commission. Compliance with consent requirements and confidentiality of participants’ data are guaranteed, with additional checks planned in the event of non-compliance or problems detected.

